**Sex**, ***n*****(%)**
Men	9,917 (49.9)	18,794 (45.0)
Women	9,958 (50.1)	22,986 (55.0)
**Age**, ***n*****(%)**
18–20 years	1,211 (6.1)	3,519 (8.4)
20–30 years	3,719 (18.7)	9,367 (22.4)
30–40 years	3,202 (16.1)	6,823 (16.3)
40–50 years	2,991 (15.1)	6,560 (15.7)
50–60 years	3,678 (18.5)	7,816 (18.7)
60–70 years	3,098 (15.6)	4,697 (11.2)
70–80 years	1,525 (7.7)	2,252 (5.4)
80+ years	451 (2.3)	746 (1.8)
**Year-quarter of test**, ***n*****(%)**
2nd 2020^*^	361 (1.8)	49 (0.1)
3rd 2020	2,267 (11.4)	716 (1.7)
4th 2020	5,718 (28.8)	12,060 (28.9)
1st 2021	4,255 (21.4)	9,341 (22.4)
2nd 2021	3,635 (18.3)	9,561 (22.9)
3rd 2021	2,483 (12.5)	6,106 (14.6)
4th 2021^**^	1,156 (5.8)	3,947 (9.4)

^*^From June 2020.

^**^Until November 2021.

### 2.3 Recruitment

Emails to invitees were send between 17 and 25 November 2021. Invited for participation were 41,780 PCR COVID-19 positives and 19,875 negatives from test records registered in the registry. Invitees received an email containing the invitation for participation, study information with a link to the website (containing the participant information and email address in case of questions), and a weblink to the online questionnaire.

Participants needed to be able to understand, read and write the Dutch language, as all materials were provided in Dutch.

Digital informed consent was asked before the questionnaire started. Further digital informed consent was asked to link data from the questionnaire to the registry data (age, sex, municipality, date of test, and test result).

A reminder was sent 1 and 3 weeks after the invitation to invitees who did not respond to the invitation or started but not completed the questionnaire. The questionnaire was made available using the MWM2 application of market research platform Crowdtech (ISO 27001 certified).

### 2.4 Inclusion

Participation started after informed consent was obtained online. Filling out the baseline questionnaire took ~30–45 min. To motivate completion of the questionnaire, participants could stop interim and complete the questionnaire at a later time.

### 2.5 Data collection

Data are collected by online self-administered questionnaires. The baseline questionnaire could be filled in between 17 November 2021 until 9 January 2022. The questionnaire contained a range of factors, including health-factors and health-conditions (Table 2). At baseline, information on the current situation as well as historical information (such as symptoms between the test and the current date) was collected from the participants. Several in-depth questions were only deemed relevant for positives or negatives, and thus not asked to all participants to minimize unnecessary load.

**Table 2 T2:** Topics and questions implemented in the questionnaire of the baseline recruitment of the prevalence, risk factors and impact evaluation of post-COVID-19 condition (PRIME post-COVID) study.

**Topic**	**Questions**	**Asked to**
Demographics	Sex	All
	Year of birth	All
	Postal code	All
	Residential situation	All
	Relationship status	All
	Level of education	All
	Country of birth	All
COVID-19 test data	Test result	All
	Test date	All
	Vaccination status	All
	Vaccination date(s)	All
	Vaccination type(s)	All
	Presence of antibodies	Negatives
Experienced symptoms	Symptoms when tested	All
	Symptoms now	All
	Severity of symptoms	All
	Duration of symptoms	All
	Course of symptoms	Positives
	Subjective assessment of degree of recovery	Positives
	Subjective assessment of having post-COVID-19 condition	Positives
Use of professional medical care	Treatment when tested (hospitalization, duration, and oxygen use)	Positives
	Received care since test	All
	Reason for received care	Positives
Lifestyle	Smoking and substance	All
	Physical activity [international physical activity questionnaire; IPAQ (26)]	All
Experienced physical and mental health	Underlying disease	All
	Origination of underlying disease	All
	Overall general health	All
	Quality of life [EQ-5D-5L (27)]	All
	Dyspnoea [modified Medical Research Council; mMRC (28)]	All
	Fatigue [checklist individual strength—subscale subjective fatigue; CIS (29)]	All
	Mental fatigue [self-constructed based on CIS-Fatigue (30)]	All
	Coping [cognitive emotion regulation questionnaire; CERQ (31)]	All
	Trauma [PTSD checklist for the DSM-5; PCL-5 (32)]	Positives
	Depression [patient health questionnaire-9; PHQ-9 (33)]	All
	Loneliness [De Jong-Gierveld (34)]	All
Labor participation	Labor participation [work productivity and activity impairment; WPAI (35)]	All
Social participation	Membership to clubs	All
Structural and functional social network characteristics assessed with name generator method (36)	Type and number of network members (family, friends, acquaintances, neighbors, colleagues, clubmates, caregivers, others)	All
	Social support of each member	All
	Type of relation with each member	All
	Social strain	All
	Age of each member	All
	Sex of each member	All
	Residential distance of each member	All
	Type of contact with each member	All

Question asked to participants tested positive or negatives for COVID-19 only was done using referral based on self-reported test result in questionnaire.

Linkage of questionnaire and registry was done by unique email address, by the data manager. For data storage and analyses, each participant has a unique study code under which all data (questionnaires and registration data) are handled.

#### 2.5.1 Prospective element: Follow-up

Follow-up measures are planned roughly each 6 months, with the option of in-between measures to assess emerging topics. All questionnaires include topics on demographics, COVID-19 test data, experienced symptoms, use of care, lifestyle, experienced physical and mental health, and labor and social network and social participation (Table 2). Additions will be made to the follow-up questionnaires, based on new insights in literature and emerging findings of data analyses.

### 2.6 Data analysis

#### 2.6.1 Primary outcomes in analysis

The time frame for collecting the primary outcomes (summarized below) runs from the baseline questionnaire up to at least 2 years thereafter, assessed at regular intervals.

The main primary outcome:

Post-COVID-19 condition: the symptoms that are defined by the WHO-definition of post-COVID-19 condition, as well as other types of definition. These include a range of symptoms measured at various time points, for example, the presence of at least one symptom 3 months after testing or when filling in the questionnaire, and experiencing of dyspnea (modified Medical Research Council; mMRC) or fatigue (Checklist Individual Strength—subscale subjective fatigue; CIS).

Other primary outcomes include:

Mental health: negative health outcomes related to mental health such as depression (assessed by PHQ-9 scale) and trauma.Social health: negative health outcomes related to social health, such as loneliness (assessed by De Jong-Gierveld scale).Physical health: negative health outcomes related to physical health such as non-communicable chronic diseases (assessed upon self-report on a checklist of conditions present), health index/quality of life (assessed by EQ-5D-5L) and physical activity (assessed by IPAQ).Positive health: experienced general health (assessed by 5-point scale ECHI).

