## 1. Introduction

Since 2020, the severe acute respiratory syndrome coronavirus-2 (SARS-CoV-2), causing coronavirus disease 2019 (COVID-19), has been disruptive to societies, globally. By August 2022, over 596 million confirmed cases were counted, accompanied by ~6 million deaths worldwide (1). An acute infection can be diagnosed using Polymerase Chain Reaction (PCR) testing and often presents with symptoms such as fever, cough, tiredness, and loss of taste or smell (2). The majority of the infections progress with mild symptoms and only few (up to a maximum of 20% in elderly) infected individuals require hospitalization (3, 4). Overall, men, people with more comorbidities, older age, and higher body mass index more frequently suffer a severe course of infection, resulting in a higher risk of hospitalization and dying as a consequence of COVID-19 (5, 6).

After great efforts to cope with new waves of SARS-CoV-2 infections globally, the Omicron wave had initially pointed to some hope of ending the pandemic (7), although situations may change quickly. Of an emerging concern are persistent symptoms after a SARS-CoV-2 infection (8–10). These persistent symptoms after COVID-19 are referred to as the patient-initiated term “long COVID” (11), “*a condition whereby affected individuals do not recover for several weeks or months following the onset of symptoms suggestive of COVID-19”* (12). As a global and standardized clinical case definition is lacking and various terminology is used to describe the same condition (13), the World Health Organization (WHO) released the term “post-COVID-19 condition” and a corresponding case definition. The WHO defined “post-COVID-19 condition” in October 2021 as “*a condition that occurs in individuals with a history of probable or confirmed SARS-CoV-2 infection, usually 3 months from the onset of COVID-19 with symptoms, that last for at least 2 months, and cannot be explained by an alternative diagnosis*” (14). Due to the high numbers of SARS-CoV-2 infections worldwide, post-COVID-19 condition poses a potential public health problem with a substantial impact on the socio-economic, emotional, and physical functioning of many individuals.

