### 2.2 Study population

The target population consisted of adults tested for COVID-19 at the GGD South Limburg with a valid PCR test result (positive/negative). We here describe the recruitment of people tested between 1 June 2020 and 1 November 2021. The GGD South Limburg tested 472,982 adults in this period. Eligible for participation were tested adults (18+ years) with a registered email address available. Of eligible adults, all people with a positive COVID-19 PCR test, and a sample of people with a negative COVID-19 PCR test were selected. All positives who met the inclusion criteria were invited to obtain a representative sample of all positives in the test registry. A reasonable sample of ~20,000 negatives were additionally included (ratio 2:1). Regarding the positives, when a person had tested positive multiple times, the record of the first positive COVID-19 test was used in the analyses, as we intended to include data on the first exposure. Regarding the negatives, a sample of people with a negative PCR test were randomly selected in each strata with a distribution that matched (1:2) positives; strata included combinations of age (18–20, 20–30, 30–40, 40–50, 50–60, 60–70, 70–80, and 80+ years), sex (man, woman), year-quarter of 2020 and 2021 in which PCR test was performed, and municipality of residence (*n* = 16) (Table 1). When tested negative multiple times, the information regarding the last negative COVID-19 test was used to have the greatest assurance that an invited control was not infected up to the point of inclusion. This procedure allowed to include a group of negatives, similar to the positives regarding sociodemographic and timing of testing.

**Table 1 T1:** Descriptives of invitees of the prevalence, risk factors and impact evaluation of post-COVID-19 condition (PRIME post-COVID) study.

**Test result, *n* (%)**	**Invitees** ***n*** = **61,655**	
	**Negative**	**Positive**
	19,875 (32.2)	41,780 (67.8)

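### One example definition under the main primary outcome counts current symptoms at baseline with no minimum time since the test, so acute or recovering illness can be counted as post-COVID-19 condition

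*Protocol article*

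**What the plan says.** Section 2.6.1 describes the main primary outcome as "the symptoms that are defined by the WHO-definition of post-COVID-19 condition, as well as other types of definition". It then illustrates the range of symptom-based definitions, giving as an example "the presence of at least one symptom 3 months after testing or when filling in the questionnaire". The first time point fixes an interval since the test; the second does not.

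The Introduction cites the WHO case definition, whose timing part reads "usually 3 months from the onset of COVID-19 with symptoms, that last for at least 2 months".

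Three other statements fix how soon after the test a participant could answer:
- Section 2.2: "We here describe the recruitment of people tested between 1 June 2020 and 1 November 2021".
- Section 2.3: "Emails to invitees were send between 17 and 25 November 2021".
- Section 2.5: "The baseline questionnaire could be filled in between 17 November 2021 until 9 January 2022".

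Section 2.2 sets no minimum time between test and invitation. Section 2.7 names one sensitivity analysis, restriction to the highest certainty score, and it does not concern timing. Section 3.1.1 discusses people tested long ago, because of recall, but not people tested very recently.

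**The concern.** A symptom reported two or three weeks after a positive test is ordinary acute or convalescent illness. It cannot show persistence at 3 months or a duration of 2 months. If current symptoms at baseline define a case with no time restriction, the prevalence estimate mixes acute with long-term symptoms.

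Three planned results are exposed:
- **Prevalence**, the first study question, is inflated if symptoms are more common before 3 months than after.
- **The background comparison** with negatives is uneven, because a larger share of positives than of negatives was tested recently.
- **Risk-factor models** that use this definition would have their early cases concentrated in the latest test dates. Vaccination status and virus variant, both named as risk factors of interest, can be expected to vary with test date.

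**Working it through.** **Inputs.** From Table 1, positives: 6,106 tested in the 3rd quarter of 2021, 3,947 in the 4th quarter (until November), 41,780 in total. Negatives: 2,483, 1,156 and 19,875. Dates are from sections 2.2, 2.3 and 2.5.

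**The plan's own figures.** The positive quarter counts sum correctly: 49 + 716 + 12,060 + 9,341 + 9,561 + 6,106 + 3,947 = 41,780, which agrees with section 2.3 ("Invited for participation were 41,780 PCR COVID-19 positives and 19,875 negatives"). The negative counts sum to 19,875. The percentages also reproduce: 6,106/41,780 = 14.6% and 3,947/41,780 = 9.4%. The article states no share under 3 months, so there is no figure of that kind to reproduce.

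**Interval limits.** Last test date to opening day: 1 November to 17 November 2021 = 16 days. Last test date to closing day: 1 November 2021 to 9 January 2022 = 69 days. Someone tested on 1 November could not reach 3 months at baseline on any permitted date.

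**Share under 3 months.** The cut-off is the completion date minus 3 calendar months. For completion in November or December 2021, everyone tested in the 4th quarter is under 3 months, together with the part of the 3rd quarter after the cut-off:

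share = [4th-quarter count + 3rd-quarter count × (days after cut-off / 92)] / total

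This assumes an even spread of tests within the 3rd quarter. The last row needs the same assumption for October.

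| All answer on | Cut-off | Positives under 3 months | Share |
|---|---|---|---|
| 17 Nov 2021 | 17 Aug | 3,947 + 6,106 × 44/92 = 6,867 | 16.4% |
| 1 Dec 2021 | 1 Sep | 3,947 + 6,106 × 29/92 = 5,872 | 14.1% |
| 15 Dec 2021 | 15 Sep | 3,947 + 6,106 × 15/92 = 4,943 | 11.8% |
| 9 Jan 2022 | 9 Oct | 3,947 × 22/31 = 2,801 | 6.7% |

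Counting 1 November as a test day changes the last row to 3,947 × 23/32 = 2,837, or 6.8%.

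Negatives on 1 December: (1,156 + 2,483 × 29/92)/19,875 = 1,939/19,875 = 9.8%.

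**Without the even-spread assumption.** The quarter totals alone bound the 17 November figure between 3,947/41,780 = 9.4% (none of the 3rd quarter after the cut-off) and (3,947 + 6,106)/41,780 = 24.1% (all of it). For the last day they bound it between 0 and 9.4%.

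**Effect on prevalence (illustration only).** If s is the share under 3 months, the pooled proportion with a symptom exceeds the proportion among those past 3 months by s × (early rate − late rate). The article gives neither rate. With an assumed late rate of 25% and early rate of 50%, the pooled figure is 25% + 0.141 × 25% = 28.5% at the 1 December share and 25% + 0.067 × 25% = 26.7% at the last-day share. With early rates of 40% and 60% at the 1 December share it is 27.1% and 29.9%.

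**The case against.** The strongest reply is that the wording is one illustration. The WHO definition is named first, study question 1 asks for prevalence by various definitions, and section 3.1 plans to compare the definitions with each other and with WHO's. A non-WHO definition that differs from WHO's is therefore not in itself a contradiction, and WHO's own 3 months is qualified by *usually*. This stands. A reader might infer that the main outcome as a whole counts any current symptom as post-COVID-19 condition; the text does not support that. What remains is that this definition sits under the post-COVID-19 label with no time rule.

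A second reply is that test date, current symptoms and symptom duration are asked of everyone (Table 2), so timing can be applied in analysis. That shows the remedy is feasible; nothing in the article says it will be applied.

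A third reply is that negatives were sampled by year-quarter of test and that section 2.7 lists year-quarter as a possible confounder. This helps the comparison of positives with negatives. It does not change the prevalence estimate, it does not turn an early symptom into a persistent one, and the 3rd quarter of 2021 straddles the 3-month line for completion dates up to late December.

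It may also be said that an unseen analysis plan could hold the restriction. Analysis-set detail does belong there, but here the article itself states the untimed alternative.

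Two further inferences should not be drawn:
- A reader might conclude that people infected before baseline would wrongly appear as incident cases at follow-up. Section 2.7 defines incidence as newly meeting the criteria since baseline, so someone who first meets a 3-month criterion after baseline is legitimately incident for the condition.
- A reader might conclude that, at baseline, time since test and test date are too nearly collinear to separate. The article gives no distribution of completion dates, so the strength of that relation cannot be established from it.

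**Conclusion.** The point holds, confined to the definition based on symptoms at questionnaire completion. As worded, it admits symptoms from 16 days after the test, and no section restricts or separates the recently tested.

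On the even-spread assumption, between 6.7% (all answering on the last day) and 16.4% (all on the first) of invited positives would be under 3 months at baseline. Reminders 1 and 3 weeks after the invitation make late November to mid-December a plausible centre, at about 12–15%. A reader might infer that one in six positives could not have reached 3 months at baseline. That figure is the opening-day ceiling; the share unable to reach 3 months on any permitted date is about 1 in 15.

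These are shares of invitees: the number of respondents and their completion dates are not given. Time is counted from the test, whereas WHO counts from onset, so the shares under 3 months from onset would be somewhat lower wherever onset preceded the test. The prevalence bias cannot be fixed from the article. The illustration of about 2 to 5 percentage points rests entirely on assumed symptom rates and on use of the definition without restriction.

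**What to change.** Where current symptoms define post-COVID-19 condition, in prevalence estimates and in risk-factor models, restrict both numerator and denominator to participants whose questionnaire date is at least 3 months after the test date. Apply the rule to positives and negatives alike. Report symptoms among those tested more recently separately, without the post-COVID-19 label, and assess these participants for the condition at the first follow-up. Apply the same rule to later recruitment periods, where the same short intervals could recur.

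The change needs analysis-set wording only: test dates are recorded, and no new data are required. The cost is that roughly 7–16% of positives, depending on when they answered, leave the baseline estimate until the next wave, planned at about 6 months. Baseline precision falls slightly, and the baseline estimate says less about the most recent infections.

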#### 2.6.2 Certainty assessment

Data on age, sex, and test result provided in the questionnaire was linked back to this data as recorded in the registry from the corresponding email address, for purposes of certainty assignment, i.e., the likelihood that the respondent indeed was the intended invitee (Figure 2). Respondents were assigned a certainty score 0 (most likely the intended invitee) when respondents consented to link questionnaire and registry data on age, sex, and test result, and this data was the same. Score 1 was given when only the test result was discrepant. Participants who did not consent to link questionnaire and registry data were assigned with score 2. Score 3 was assigned to respondents who did not match on sex or age, representing probably another person than the intended invitee.

**Figure 2 F2:**
[figure not shown]
Decision tree to ascertain certainty assessment scores based on self-reported and public health registry data.

Furthermore, it cannot be formally ruled out that the negative PCR-tested participants, who also did not report COVID-19 antibodies pre-vaccination, might include some COVID-19 positive cases. The absence of SARS-CoV-2 antibodies does not guarantee that an infection did not take place since some people (often mild cases) do not show sero-conversion and also sero-reconversion occurs over time (37–40). We will take reported antibody status in PCR negatives into account when estimating the prevalence of experienced symptoms.

#### 2.6.3 Missing data and data cleaning

The questionnaire started with collection of clinical and demographical data. Participants who did not fill in these topics had insufficient data for any of the planned analyses. The remaining participants were categorized based on extent to which they completed the rest of the questionnaire. All questions were mandatory, therefore no missing data had to be handled and no imputation methods were used.

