#### 3.1.2 Prospective element

The major strength of the prospective assessments is the opportunity to study changes in outcomes and determinants before, during, and after (re)infection. Causal hypotheses can be considered, as the order of observations is equal to the natural course of events over time. Besides, overall PCR test data (from June 2020 onwards) can be accessed from the public health registry as well, to gain a reliable estimation of total exposure (i.e., the total number of positive tests/re-infections). Furthermore, the inclusion of new participants tested in later calendar periods (open cohort design) is of great value to study the prevalence of post-COVID-19 condition in the context of new emerging virus variants. In addition, it is predicted that the proportion of test-negative controls declines over time, due to acquired infection. The prospective aspect enables us to include supplemental controls to maintain a sufficient number of test-controls.

Attrition bias is the major limitation of the prospective element to be acknowledged. Selective withdrawal might occur when participants are physically unable to complete follow-up questionnaires, due to severe illness for example. This disproportional attrition threats the internal validity and might lead to underestimation or overestimation of prevalence estimates or associations (43). In general, we will consider the described limitations in the interpretation of our results, and when possible, take them into account in analysis.

To conclude, the PRIME post-COVID longitudinal study design holds several considerable strengths, such as the mapping of a wide variety of physical, emotional, social, and behavioral aspects, and including a population-based sample additionally comprising PCR negatives. Results of our study will contribute to the further characterization of post-COVID-19 condition and thereby inform practical guidance for society, and clinical and public health practice for the prevention and care for long-term impact of COVID-19.

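### Mandatory questions do not rule out missing data: break-off in the baseline questionnaire leaves the later scale outcomes observed only in those who reached them

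*Protocol article*

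**What the plan says.** Section 2.6.3 (Missing data and data cleaning) makes four statements in sequence:

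- On order: "The questionnaire started with collection of clinical and demographical data".
- On those who did not get through that opening part: "Participants who did not fill in these topics had insufficient data for any of the planned analyses".
- On everyone else: "The remaining participants were categorized based on extent to which they completed the rest of the questionnaire".
- The conclusion: "All questions were mandatory, therefore no missing data had to be handled and no imputation methods were used".

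Two earlier sections bear on this. Section 2.4 says of the length "Filling out the baseline questionnaire took ~30–45 min", and that "participants could stop interim and complete the questionnaire at a later time". Section 2.3 sends reminders to "invitees who did not respond to the invitation or started but not completed the questionnaire".

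Section 2.6.1 places mMRC dyspnoea and CIS fatigue among the possible definitions of the main primary outcome. It lists depression (PHQ-9), trauma, loneliness, EQ-5D-5L, IPAQ and general health among the other primary outcomes.

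**The concern.** The last statement of section 2.6.3 does not follow from its premise and conflicts with the statement before it. If participants differ in how far they got, everything beyond each person's stopping point is missing for that person. Making items compulsory removes one kind of missingness (skipped items) and leaves the other (break-off) untouched.

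This is more than a detail left for an analysis plan. The article gives a reason why nothing needs handling and settles the method on that basis. Followed as written, each later scale is analysed in whoever reached it, and the result is described as free of missing data.

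Break-off need not be unrelated to the outcomes. Fatigue and mental fatigue are measured in this study and could plausibly stop someone finishing a long form. Equally, people troubled by lasting symptoms may be more motivated to finish. Table 2 also shows more items put only to positives (such as course of symptoms, recovery and trauma) than only to negatives (antibodies), so completion could differ by test result. At stake are the prevalence of the scale-based outcomes and the comparison of positives with negatives.

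**Working it through.** **Figures in the document.** The article gives no response rate, completion rate or expected prevalence, so there is no stated figure to reproduce on this point. The invitation counts are consistent: 41,780 + 19,875 = 61,655, which is 67.8% and 32.2% as in Table 1. Everything below uses assumed inputs and only illustrates how large the effect could be.

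**1. Prevalence among those who reach the scale.** Let p be the true prevalence among starters, and c1 and c0 the completion shares in those with and without the outcome. The prevalence seen is

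p·c1 / (p·c1 + (1 − p)·c0).

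With p = 20%:

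| c1 (with outcome) | c0 (without) | Calculation | Prevalence seen |
|---|---|---|---|
| 80% | 80% | 0.16 / (0.16 + 0.64) | 20.0% |
| 70% | 80% | 0.14 / (0.14 + 0.64) | 17.9% |
| 60% | 80% | 0.12 / (0.12 + 0.64) | 15.8% |
| 80% | 70% | 0.16 / (0.16 + 0.56) | 22.2% |
| 80% | 60% | 0.16 / (0.16 + 0.48) | 25.0% |

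The error is zero when completion is unrelated to the outcome and can go either way when it is related.

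**2. Worst-case bounds.** If 20% is observed in a share c who completed, the prevalence in all starters lies between 0.20·c and 0.20·c + (1 − c):

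- c = 95%: 19% to 24%
- c = 90%: 18% to 28%
- c = 80%: 16% to 36%

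**3. Positives against negatives.** With no true difference, selection alone gives an odds ratio of (c1/c0 in positives) / (c1/c0 in negatives):

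- Positives 80%/70%, negatives 70%/70%: (0.80/0.70) / (0.70/0.70) = 1.14
- Positives 80%/70%, negatives 70%/80%: (0.80/0.70) / (0.70/0.80) = 1.31
- Positives 70%/80%, negatives 75%/75%: (0.70/0.80) / (0.75/0.75) = 0.87 (0.875 before rounding)

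If the ratio c1/c0 is the same in both groups, the odds ratio is not distorted, even though each prevalence may be.

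**4. Scale against sampling error.** At 20% with an assumed n = 5,000, the 95% half-width is 1.96·√(0.2·0.8/5,000) = 1.1 percentage points. A shift of about 2 points, as in the 70%/80% rows, would be larger than the stated uncertainty.

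**The case against.** Several objections have force and limit the point.

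- **Partial completion is disclosed.** Sections 2.3, 2.4 and 2.6.3 all mention it, and the sentence on mandatory questions can be read as covering skipped items only. A reader might infer that the plan prescribes an analysis of full completers. It does not: grading by extent of completion fits an available-case set per outcome equally well. The sentence is nevertheless not worded as being about skipped items, and it rules out any handling.
- **Save-and-resume and the reminders reduce break-off.** That is so, and section 2.4 gives encouraging completion as the purpose. They lessen the problem without removing it, since the article still sorts people by how far they got.
- **Weighting is mentioned.** Section 3.1 proposes, as an example, weighting subgroups to the invited population when estimating prevalence, and plans to examine whether associations differ across subgroups. A reader should therefore not infer that no adjustment of any kind was considered. But the weighting is only an example, concerns prevalence and representation relative to invitees, and is not built on completion status.
- **Follow-up attrition.** A reader might extend the point to later waves. The text does not support that: section 2.6.3 is in the past tense and describes the baseline questionnaire, while section 3.1.2 openly says "Selective withdrawal might occur when participants are physically unable to complete follow-up questionnaires, due to severe illness for example" and calls attrition the major limitation of the prospective part.
- **Symptom-based definitions.** If symptoms were part of the opening clinical block, definitions resting on at least one symptom are largely protected. The article does not say exactly what that block held, nor the order of the later scales. Table 2 suggests an order but does not state one.
- **Direction of bias.** It is tempting to conclude that fatigue is underestimated because fatigued people stop. No completion data support that, and section 3.1 raises the reverse possibility for participation, namely that positives who believe they have lasting symptoms take part more often.

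**Conclusion.** The statement that mandatory questions left no missing data to handle is wrong on the article's own account of partial completion, and it fixes the method for baseline outcomes measured after the opening block. Estimates for these outcomes, and the positive–negative contrast based on them, may be biased. Under assumed completion of 60–80%, a true 20% could be reported as anything from about 16% to 25%, and spurious odds ratios of 0.87 to 1.31 arise in the cases tried. If completion is unrelated to the outcome, there is no bias.

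The internal contradiction is certain. The presence, direction and size of bias are not, and they depend on completion rates by outcome and test result that the article does not report. The point is confined to baseline break-off and to outcomes collected after the opening block.

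**What to change.** 1. Reword the last sentence of section 2.6.3 so that it claims only that no items were skipped within completed sections.
2. Report how many participants completed each block, by test result and by symptom status from the early questions, and compare full with partial completers on the opening-block data.
3. State the analysis set for each outcome.
4. For outcomes after the opening block, use inverse-probability-of-completion weighting or multiple imputation. Base it on opening-block and registry variables: test result, age, sex, municipality, year-quarter of test, and vaccination and symptoms where these were collected early. For participants who did not consent to registry linkage, use the self-reported values. Keep the available-case analysis as a sensitivity analysis.

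The cost is a change of wording, some added tables and modest programming. No new data are needed. The price is reliance on data being missing at random given the early answers. This cannot be verified, and it could fail if an unmeasured worsening both stops people and drives the outcome.
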